## Methods/design

PACE-D is a pragmatic non-randomised controlled trial that evaluates the effects of personalised CSP on persons living with diabetes over two annual reviews with two groups: Intervention experiences personalised CSP; and Control continues with the current care model. Figure 1 illustrates the flow diagram for study participants.

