### Study setting

PACE-D is conducted in the polyclinics at National University Polyclinics (NUP), the westernmost of three major administrative primary care healthcare groups in Singapore. Each polyclinic is staffed by 15–25 primary care physicians (PCPs) deployed in multi-disciplinary teams which include nurses and clinical pharmacists, with access to the psychologist, dietitian and medical social worker. In addition to the management of acute episodic conditions, the polyclinics provide for the efficient care of the patient with LTCs: laboratory services allow for rapid investigative reporting; surveillance programmes ensure the systematic detection of diabetic retinopathy, neuropathy and nephropathy; and workflows designed to target specific needs through the use of teamlets, [24] tele-consults, [25] and multidisciplinary case discussions [26, 27].

At the polyclinics under NUP, primary care is delivered to patients with LTCs through care teams known as teamlets. Each teamlet provides LTC care to a regular pool of approximately 5000 patients. It is formed by two PCPs and one care manager (CM) who is a chronic disease management-trained senior nurse. These three HCPs are supported by a care coordinator (CC) who schedules consultation and preventive health screening appointments for teamlet-empanelled patients.

In PACE-D, four of the six NUP polyclinics are involved in the study, with two of them designated as Intervention and the other two as Control. In each of these polyclinics, one teamlet is involved in the study and is supported by a PACE-D Coordinator (PC). The role of the PC is to recruit participants and obtain consent for participation, prepare the care planning letter (CPL) for mailing to the participants in the Intervention, and to administer questionnaires to all participants.

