## Sample size calculation

The sample size calculation was based on HbA1c, the primary outcome measure, for which a difference of 0.5 percentage points was taken to be clinically meaningful. The sample size of 1620 was calculated based on 1:1 allocation into the Intervention and Control, 6 pre-specified subgroups (with 3 age tertiles and 2 gender groups), at a power of 90%, with an alpha value of 0.05 (95% confidence interval) and accounting for an attrition rate of 30%. The study team aims to recruit a total of 1620 patients across the four sites.

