## Statistical methods

### Statistical analyses

Descriptive statistics of the baseline data will be reported, and exploratory data analysis will be conducted prior to model building. Continuous variables will first be tested for normality of distribution. Bivariate analyses will be conducted for continuous variables, and chi-squared test or Fisher’s exact test for categorical variables will be used to determine statistically significant differences between the Intervention and the Control for each baseline characteristic. The analysis will be conducted with the intention-to-treat (ITT) principle unless otherwise specified. Missing endpoints will be imputed with the last observation carried forward (LOCF).

Generalised linear regression will be used to analyse the study endpoint (HbA1c) and while controlling for baseline HbA1c as a covariate. PAM-13 score and other secondary continuous outcomes variables will follow the same analysis methods unless otherwise stated. Logistic regression will be utilised to assess binary outcomes such as screening compliance in the past year, smoking status, and frequent exercise status. Covariates and interaction terms to be included in the model will be selected through inquiry of the data and reviewing existing literature. A stepwise process will be used to drop covariates that have a *p*-value greater than or equal to 0.2. Akaike information criterion (AIC) will be used to decide on the linear model used for potentially non-normal dependent variables such as total cost. Covariates included in the various models will be reported. The outcomes will be compared between the Intervention and the Control. Statistical tests will be conducted at a 2-sided alpha level of 0.05 with confidence intervals calculated at 95%, 2-sided unless otherwise stated. All analysis will be conducted using the STATA software version 16.

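### Treatment is assigned by polyclinic, two per arm, but the stated primary regression does not provide for clustering, so its 5% test and 95% interval fail if any between-clinic correlation remains

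*Protocol article*

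**What the plan says.** - **Allocation.** The Study setting section of the protocol article says "four of the six NUP polyclinics are involved in the study, with two of them designated as Intervention and the other two as Control". It adds "In each of these polyclinics, one teamlet is involved in the study", with one coordinator per site. Clinic, teamlet and coordinator are therefore the same four clusters, nested within arm.
- **Design.** Methods/design: "PACE-D is a pragmatic non-randomised controlled trial that evaluates the effects of personalised CSP". The clinics were designated, not randomised.
- **Primary model.** Statistical analyses: "Generalised linear regression will be used to analyse the study endpoint (HbA1c) and while controlling for baseline HbA1c as a covariate". Further covariates come from inspecting the data, from the literature and from a stepwise rule. The analysis is by intention to treat, with LOCF for missing endpoints.
- **Error rate.** Same section: "Statistical tests will be conducted at a 2-sided alpha level of 0.05 with confidence intervals calculated at 95%, 2-sided unless otherwise stated".
- **Other outcomes.** PAM-13 and the other secondary continuous outcomes follow the HbA1c methods unless otherwise stated. Binary outcomes get logistic regression. Cost gets a gamma model with log link or a difference-in-difference analysis. Utilisation gets a Poisson or zero-inflated negative binomial model.
- **Sample size.** The 1620 rests on 1:1 allocation, six subgroups, an effect for which "a difference of 0.5 percentage points was taken to be clinically meaningful", and "at a power of 90%, with an alpha value of 0.05 (95% confidence interval) and accounting for an attrition rate of 30" per cent. No SD, ICC or design effect is given.

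The article mentions no clinic or teamlet effect, random effect, GEE or cluster-robust variance. The Subgroup analyses section lists treatment group, time, sex and age category, and no clinic term.

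**The concern.** Patients at one site share two physicians, a care manager, a coordinator and local practice. The treatment contrast compares two such groups with two others. A regression that takes patients as independent gives that contrast the precision of some 1,600 separate observations. Any drift in HbA1c that belongs to a clinic (prescribing, staffing, workflow) is then read as a treatment effect with that precision. Baseline adjustment removes differences in starting level but not differences in change during follow-up. At stake is whether an ordinary difference among four clinics could be reported as a significant effect of care and support planning.

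**Working it through.** **1. The plan's own figure.** The SD is not stated, so 1620 can only be back-solved. Two arms by six subgroups give 12 cells: 1620/12 = 135 per cell, and 135 × 0.7 = 94.5 evaluable. With n = 2(1.96 + 1.2816)² SD²/0.5², this gives SD = 0.5 × √(94.5/2)/3.2416 = 1.06. Going forward with rounding up, SD 1.05 gives 1596 and SD 1.06 gives 1632. An individual-level formula thus accounts for 1620 at a plausible SD, with no design effect in it. Inflating by 1.3 instead of dividing by 0.7 would imply SD 1.11.

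**2. Cluster size.** 1620/4 = 405 per clinic, assuming equal clinics. This is the nearer figure for the planned analysis (intention to treat with LOCF). Completers only would be 405 × 0.7 = 283.5.

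**3. Inflation.** Design effect DE = 1 + (m − 1) × ICC. True type I error of the nominal 5% test = 2[1 − Φ(1.96/√DE)]. The ICC that matters is that of baseline-adjusted HbA1c. It is not given, so a range is assumed. Example at m = 405, ICC 0.01: DE = 1 + 404 × 0.01 = 5.04, √DE = 2.24, error 38%.

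| Assumed ICC | DE, m = 405 | Error, m = 405 | DE, m = 283.5 | Error, m = 283.5 |
|---|---|---|---|---|
| 0.001 | 1.40 | 10% | 1.28 | 8% |
| 0.005 | 3.02 | 26% | 2.41 | 21% |
| 0.01 | 5.04 | 38% | 3.83 | 32% |
| 0.02 | 9.08 | 52% | 6.65 | 45% |
| 0.05 | 21.2 | 67% | 15.1 | 61% |

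A simulation of four clusters of 284 patients (20,000 runs per ICC) gave 5.1% at ICC 0, then 8.1%, 20.8%, 31.5%, 44.8% and 61.6%. In the same runs a t-test on the four clinic means, with 2 df, held 4.7% to 5.1%.

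**4. What a clinic-level inference costs.** Four clinics in two arms leave 4 − 2 = 2 df, with critical t 4.303. With assumed SD 1.06 and m = 405, the naive SE is 1.06 × √(4/1620) = 0.053, half-width 1.96 × 0.053 = 0.10. At ICC 0.01 the SE is 0.053 × 2.24 = 0.118, half-width 4.303 × 0.118 = 0.51.

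| Assumed ICC | Half-width, points | Power for 0.5 points (2 df) |
|---|---|---|
| 0.001 | 0.27 | 96% |
| 0.005 | 0.39 | 78% |
| 0.01 | 0.51 | 60% |
| 0.02 | 0.68 | 41% |
| 0.05 | 1.04 | 23% |

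**5. Can the open parts of the plan repair it?** Arm is the sum of two of the four clinic indicators, so a full set of fixed clinic effects leaves the treatment effect unidentified. Stepwise selection of covariates is not a method for clustering. Robust variances without a small-sample correction remain anti-conservative with four clusters. In a random-intercept model the clinic variance is often estimated as zero: the chance is about 1 − exp(−1/DE), which at m = 283.5 is 23% for ICC 0.01 and 54% for ICC 0.001.

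**The case against.** The article is a condensed account. It names a regression family and an alpha but no variance estimator, and it leaves covariates open. A cluster-adjusted variance could stand in an analysis plan that is not shown. A reader might infer that the trial has decided to ignore clustering; the text is silent and does not say that. The point still stands, because the article does fix the primary model and the error rate, and the additions its wording leaves room for (clinic as a covariate, a robust variance) do not work with two clinics per arm.

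A reader might also infer that the standard errors are certainly too small, and by a known factor. The documents do not support that either. The inflation depends on a residual ICC that they do not give. At ICC 0.0001 and 283.5 per clinic the error is only 5.3%, which is negligible.

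Nor does one model serve every outcome. Only PAM-13 and the other secondary continuous outcomes inherit it. The binary, cost and utilisation models are different, though they too state no handling of clinic.

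Finally, the clinics were designated. A 2-df test treats them as exchangeable draws, which they may not be, and it does nothing about systematic differences between them. That limits what the remedy achieves but does not justify patient-level precision.

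**Conclusion.** The concern holds in conditional form. The stated primary analysis does not match the unit of allocation. For any positive between-clinic correlation left after baseline adjustment, its standard errors are too small and the nominal 5% and 95% do not hold. The direction follows from the design; the size rests on an assumed ICC. Over 0.001 to 0.05, the standard error at 405 per clinic is too small by a factor of about 1.2 to 4.6 (√1.40 to √21.2). These figures assume equal clinic sizes. The half-widths and power also assume an SD of 1.06, which is back-solved from 1620 and not stated in the article. Because the clusters are so large, an ICC as low as 0.001 already doubles the error rate, so this should be corrected before the analysis.

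**What to change.** Name one primary inference in the Statistical analyses section. First regress endpoint HbA1c at patient level on baseline HbA1c and covariates fixed in advance, without the treatment term. Then average the residuals within each polyclinic and compare the four means, two against two, with a t-test on 2 df and the matching 95% interval. A random-intercept model should not be offered as an interchangeable alternative, given how often its clinic variance would be estimated as zero.

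Use the same clinic-level summary approach for PAM-13 and for the other continuous, binary, cost and utilisation outcomes. Report the patient-level regressions as descriptive only.

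The change is wording and a little code, with no new data. The real cost is precision: the interval widens through both the larger standard error and the critical value of 4.30, and at the higher ICCs the trial may be unable to confirm a 0.5-point difference. The plan should say so. The conclusion should state that the contrast rests on two designated, non-randomised clinics per arm, and that the variance correction leaves confounding by clinic in place.

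### Confounders in this non-randomised comparison are selected partly from the data and dropped stepwise at p ≥ 0.2, which weakens confounding control and makes the nominal error rate and intervals somewhat too optimistic

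*Protocol article*

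**What the plan says.** Methods/design states that "PACE-D is a pragmatic non-randomised controlled trial". Under Study setting, four polyclinics take part, "with two of them designated as Intervention and the other two as Control", with one teamlet in each.

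Statistical analyses gives the model for HbA1c as a generalised linear regression, "while controlling for baseline HbA1c as a covariate". No other covariate is named for it. The rest of the adjustment set is left to a procedure: "Covariates and interaction terms to be included in the model will be selected through inquiry of the data and reviewing existing literature". After that, "A stepwise process will be used to drop covariates that have a" p-value "greater than or equal to 0.2". The same section fixes two-sided tests at 0.05 and 95% intervals, with no allowance for the selection, and says that the covariates used will be reported. It also plans significance tests that "will be used to determine statistically significant differences between the Intervention and the Control for each baseline characteristic", but does not link these tests to the choice of covariates.

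Subgroup analyses carries the covariates found in model building into the subgroup model. The false discovery rate correction there concerns the subgroup tests.

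**The concern.** Clinics were designated, not randomised, so differences in patient mix between the clinics become differences between the arms. For the primary outcome, the regression covariates are the main statistical means of dealing with this.

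The bias from leaving out a confounder is roughly its imbalance between arms times its effect on the outcome. Read naturally, the p-value in the drop rule is the covariate's p-value in the outcome model. That reflects strength of association and sample size, and takes no account of how far the covariate differs between arms. A weak predictor that differs clearly between clinics can therefore be dropped, and its share of the bias moves into the treatment coefficient.

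The standard error of the final model is also computed as if that model had been chosen without looking at the outcome, so it tends to be too small. Selecting interaction terms from the data adds a further choice: if a treatment interaction entered the primary model, the treatment coefficient would change its meaning. At stake are the false-positive rate and interval coverage of the primary comparison.

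**Working it through.** **Inputs from the Protocol article.** Total sample 1620, 1:1 allocation, 30% attrition, target difference 0.5 HbA1c points, two-sided alpha 0.05, drop threshold 0.2. Participants expected to have an observed endpoint: 1620 × 0.7 = 1134. Because the plan is intention-to-treat with last observation carried forward, the analysis set may be as large as 1620. Both sizes are shown.

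**The plan's own figure.** No SD is stated, so 1620 can only be back-solved. Assume full power in each of 6 subgroups × 2 arms = 12 cells. Then n per cell = 2(1.960 + 1.282)² SD²/0.5² ≈ 84.06 SD². SD 1.05 gives 93 per cell, and 93 × 12/0.7 ≈ 1595. SD 1.06 gives 95 per cell, and 95 × 12/0.7 ≈ 1629. An SD of about 1.06 is therefore compatible with 1620. The point does not depend on it.

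**Assumed inputs (none are in the document).** 12 weak confounders at 0.03-0.05 HbA1c points per SD, residual SD 1.0, baseline HbA1c always kept, no true treatment effect, independent patients and no clinic clustering.

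**How often a true confounder is dropped.** With z = β√n/σ, the chance of p ≥ 0.2 is Φ(1.2816 − z) − Φ(−1.2816 − z).

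| β per SD | n = 1134: z, P(drop) | n = 1620: z, P(drop) |
|---|---|---|
| 0.03 | 1.01, 60% | 1.21, 52% |
| 0.04 | 1.35, 47% | 1.61, 37% |
| 0.05 | 1.68, 34% | 2.01, 23% |
| 0.10 | 3.37, 2% | 4.02, 0.3% |

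The imbalance between arms does not appear in z. With residual SD 0.9 and n = 1134, the formula gives 55%, 28% and 0.7% at 0.03, 0.05 and 0.10. A separate simulation with 5 or 10 covariates found 54-56%, 28-29% and 0.6-0.8%, identical at every imbalance from 0 to 0.6 SD.

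**Bias.** Dropping a covariate shifts the treatment coefficient by about its estimated coefficient times the imbalance. The expected estimated coefficient over the drop region is (σ/√n) × {z·P(drop) − [φ(1.2816 − z) − φ(1.2816 + z)]}. At β = 0.04 and n = 1134 this is 0.0297 × {1.347 × 0.470 − [0.398 − 0.013]} ≈ 0.0074. If all 12 confounders act in one direction at 0.3 SD imbalance, the bias is 12 × 0.3 × 0.0074 ≈ 0.027. At n = 1620 it is 0.0248 × {1.610 × 0.369 − [0.378 − 0.006]} ≈ 0.0055, so 12 × 0.3 × 0.0055 ≈ 0.020. Leaving out all 12 would give 12 × 0.3 × 0.04 = 0.144.

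**Type I error, backward elimination at p ≥ 0.2 (simulation, 2000 runs per setting).**

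| Imbalance 0.3 SD | n = 1134 | n = 1620 |
|---|---|---|
| Confounders in the same direction | 9.5% (bias 0.027) | 8.2% (bias 0.017) |
| Random directions | 6.9% (bias about 0) | 7.6% (bias about 0) |
| Fixed full set | about 5% | about 5% |

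The Monte Carlo standard error near 7% is √(0.07 × 0.93/2000) ≈ 0.6 points. Allowing for repeat runs, the stepwise ranges are about 7-10% and 7-9%. At 0.2 SD imbalance the error is about 6-8%, and at 0.1 SD there is little difference.

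**Interval width.** In the separate simulation (n = 1134, 10 covariates, residual SD 0.9), covariates with no true effect at 0.4 SD imbalance gave a mean model SE of 0.056 against a true spread of 0.060. The most extreme setting (0.6 SD, β = 0.03, one direction) gave 0.063 against 0.077, with type I error 0.174.

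**The case against.** The strongest case for the plan is that 0.2 is a lenient threshold, baseline HbA1c is named in the model, and literature informs the choice. Strong confounders survive: at 0.10 per SD they are dropped 2% of the time or less. All of that stands. A reader might infer that confounding control is discarded, and the document does not support that. In the illustration, stepwise dropping leaves 0.027 of the 0.144 points that omitting all 12 confounders would leave, so about four fifths is still removed. Even the extreme setting had 0.17 type I error against 0.91 with baseline HbA1c alone.

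Other stronger readings also fail:

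- **Interactions screened at 0.2.** With 10 null candidates, at least one would be kept with probability 1 − 0.8¹⁰ = 89%. But the 0.2 rule is written for covariates, the number of candidates is not given, and the plan does not say that the interactions involve treatment. In simulation the treatment main-effect test held 0.05 when covariates were centred, and the plan does not describe the coding.
- **Different adjustment sets by outcome.** Confounders of cost, smoking and HbA1c can legitimately differ, so this is not an error in itself.
- **A selected model presented as fixed in advance.** The plan says that the covariates used will be reported. That is transparency after the event, which does not restore the error rate, but it is not concealment.
- **Adjustment as the only protection.** All clinics belong to one healthcare group and share eligibility criteria, and difference-in-difference is an option for cost.

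A separate analysis plan could list covariates. That does not answer the point, because the article states a data-driven rule and does not merely leave the matter open.

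**Conclusion.** The point holds in moderate form. The plan fixes a poor retention rule for a comparison whose arms are set by clinic. It lets imbalanced, weakly prognostic confounders be dropped and leaves tests and intervals at nominal levels after selection from the data.

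The harm is modest: type I error of about 7-10% instead of 5% at 0.3 SD imbalance, and close to nominal at 0.1 SD. Bias is at most about 0.03 HbA1c points, or 6% of the 0.5-point target, and arises only if the confounders mostly act in one direction. The error rate and interval width matter more than the bias.

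The direction is secure. The size is illustrative, because the number, strength and imbalance of the confounders and the residual SD are all assumed. The calculations treat patients as independent. With two clinics per arm, the roughly 5% for the fixed set shows what the selection rule costs and is not a prediction of the trial's actual error rate.

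**What to change.** In Statistical analyses, delete the stepwise p ≥ 0.2 rule. For the primary HbA1c model, keep baseline HbA1c and name the other confounders in advance from the items under Baseline data and questionnaire collection: age, sex, ethnicity, education, housing type, oral medication and insulin use, comorbidities, weight and smoking. Add years since diagnosis if it is captured. Subgroup analyses needs it, but it is not among the listed baseline items. Keep every named term whatever its p-value.

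Keep data-selected treatment interactions out of the primary model and confine them to the subgroup analyses. Label any data-driven model a sensitivity analysis. Other outcomes may have their own adjustment sets, provided these are also fixed in advance.

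The cost is a change of wording and some degrees of freedom. Even 20 would be 20/1134 = 1.8% of the smaller analysis set, which is negligible. Apart from confirming that years since diagnosis is recorded, no new data are needed.

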### Subgroup analyses

HbA1c levels are known to be related to gender and age amongst patients with diabetes in various population groups, which may be attributed to a multitude of factors such as biological differences and disease progression status. However, the relationship between gender and patient activation has yielded inconsistent results in various different population context [30, 31]. To elucidate these relationships under the unique context, pre-specified subgroup analysis will be conducted to evaluate HbA1c. The model for subgroup analysis would include treatment group, time, with sex and age category (3 strata, “18–49”, “50–64” & “65 and above”) as fixed effects, adjusting for covariates identified in model building. The significance will be adjusted using false discovery rate correction to account for multiple testing [32].

Exploratory analysis will also be conducted for the variables HbA1c and PAM-13 score to examine the effects of the programme across different population subgroups. The following subgroups will be assessed: ethnicity, years since diagnosis of diabetes at baseline, HbA1c at baseline, education, and baseline insulin use. The purpose of the analyses is for exploratory purposes and to guide hypothesis generation and inform subsequent research studies [33].

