## Outcome measures

### Primary outcome

Change in HbA1c levels in patients receiving the CSP intervention compared with patients receiving standard care from baseline to the study endpoint as defined by the second annual review

The latest HbA1c reading prior to the first annual review will be taken as the baseline and the HbA1c on the second annual review will be taken as the endpoint. The baseline and endpoint for the other variables will be selected on a similar basis.

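### The pre-specified subgroup model, as listed, names no treatment-by-sex or treatment-by-age term and carries a time term that does not fit the primary HbA1c model

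*Protocol article*

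**What the plan says.** The section on subgroup analyses (Protocol article) states the model for the pre-specified age and sex analysis of HbA1c: "The model for subgroup analysis would include treatment group, time, with sex and age category", with three age strata, "as fixed effects, adjusting for covariates identified in model building". On multiplicity it adds: "The significance will be adjusted using false discovery rate correction to account for multiple testing". No product of treatment with sex, age or time is mentioned.

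Interactions appear once, in the section on statistical analyses: "Covariates and interaction terms to be included in the model will be selected through inquiry of the data and reviewing existing literature". The next sentence there describes a stepwise process that drops covariates with a p-value of 0.2 or more.

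The primary analysis has a different form: "Generalised linear regression will be used to analyse the study endpoint (HbA1c) and while controlling for baseline HbA1c as a covariate". The primary outcome section defines two HbA1c readings, one before the first annual review and one at the second: "The latest HbA1c reading prior to the first annual review will be taken as the baseline and the HbA1c on the second annual review will" serve as the endpoint. The sample size section derives 1620 from six pre-specified subgroups (three age groups by two genders), a difference of 0.5 percentage points, 90% power, alpha 0.05 and 30% attrition.

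**The concern.** A subgroup analysis of a treatment effect asks whether the arm difference varies with sex or age. Main effects of sex and age answer another question: whether HbA1c itself differs by sex or age. Fitted with the listed terms alone, the model returns one treatment coefficient common to all patients.

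If the terms that carry the subgroup question are picked after looking at the data, the analysis is no longer pre-specified in the sense that matters, and the set of tests to which the false discovery rate correction applies is not fixed in advance.

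The time term raises a second difficulty. With only two HbA1c readings defined, it has meaning only if the baseline reading is an outcome row, which is not how the primary model treats it. The sections state that "PACE-D is a pragmatic non-randomised controlled trial", so the arms may differ in HbA1c at baseline, and a model that mixes baseline with endpoint would carry that difference into the treatment coefficient.

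**Working it through.** **Inputs.** Listed terms: treatment group, time, sex, age category (Subgroup analyses). HbA1c readings: baseline and endpoint (Primary outcome). Target difference 0.5, six subgroups, 1:1 allocation, 90% power, 30% attrition, total 1620 (Sample size calculation); two-sided alpha 0.05 (Statistical analyses). No standard deviation is stated.

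**1. What 1620 corresponds to.** Six subgroups in two arms make 12 cells: 1620 / 12 = 135 per arm per subgroup, and 135 x 0.7 = 94.5 evaluable. From n = 2 SD² (1.960 + 1.282)² / 0.5², the implied SD is 0.5 x sqrt(94.5 / 2) / 3.242 = 1.06. Working forward with rounding up, SD 1.05 gives 1596 and SD 1.06 gives 1632; SD 1.0 gives 1464 and SD 1.2 gives 2100. If attrition was instead applied by multiplying by 1.3, SD 1.11 gives 1632. The figure cannot be reproduced strictly without the SD, but it fits 90% power for a 0.5 difference inside each of the six subgroups.

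**2. What the listed terms estimate if both readings are outcome rows.** Let D0 be the arm difference at baseline and D1 the arm difference at endpoint. With one row per patient at each time, and treatment and time as main effects, the treatment coefficient is (D0 + D1) / 2. Take a true effect of -0.50 and let any baseline difference persist in full, so D1 = D0 - 0.50:

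| Baseline difference D0 | Endpoint difference D1 | Treatment coefficient |
|---|---|---|
| 0 | -0.50 | -0.25 |
| +0.3 | -0.20 | +0.05 |
| +0.5 | 0.00 | +0.25 |
| -0.3 | -0.80 | -0.55 |

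In the last row -0.30 of the -0.55 is imbalance, about half. If the imbalance shrinks by an assumed baseline-endpoint correlation of 0.65, D1 = -0.50 - 0.195 = -0.695 and the coefficient is (-0.30 - 0.695) / 2 = -0.50, again about half imbalance. The baseline differences are illustrations, not figures from the article.

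**3. Whether subgroup effects are recovered.** Noise-free least squares on two rows per patient, with assumed subgroup effects of -1.0, -0.8, -0.6, -0.4, -0.2 and 0.0 (mean -0.5) and no baseline difference: the listed main effects give the single coefficient -0.25, the same as when every subgroup has -0.5. Adding treatment x time x sex x age recovers all six effects exactly.

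**4. If baseline is a covariate.** Each patient then has one outcome row, at endpoint. Time is constant and has no role. There is no averaging of baseline with endpoint, but the listed terms still give one common treatment coefficient.

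**5. Power of the contrasts to be added.** Assumptions: SD 1.06, 94.5 evaluable per arm in each of six equal cells, no clustering, no multiplicity correction. SE = SD x sqrt(k / n), where k is the number of group means compared and n the patients in each.

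| Contrast | k, n | SE | Power for 0.50 | Power for 0.25 |
|---|---|---|---|---|
| Arm effect within one cell | 2, 94.5 | 0.154 | 90% | 37% |
| Arm x sex | 4, 283.5 | 0.126 | 98% | 51% |
| Arm x age, two strata | 4, 189 | 0.154 | 90% | 37% |
| Arm effect, one cell against another | 4, 94.5 | 0.218 | 63% | 21% |
| One arm x age x sex contrast | 8, 94.5 | 0.308 | 37% | 13% |

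For an interaction, 0.50 means two subgroup effects differing by as much as the whole target effect; smaller differences have much less power.

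**The case against.** The sentence says what the model would include, which need not be a complete list. It also adjusts for covariates from model building, and model building elsewhere in the article expressly admits interaction terms. A false discovery rate correction presupposes several tests, and a sample size built on six subgroups suggests that arm effects within them are wanted. A condensed sentence is a fair explanation. The full protocol and any analysis plan are not shown, and the correlation structure for repeated readings is ordinary detail for those documents.

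Most of this stands, and it rules out the stronger readings. A reader might infer that the model cannot estimate subgroup effects, or that it will return a wrong coefficient; both need the list to be exhaustive, and the second also needs stacked rows, which the article does not state. A reader might also infer that the trial was enlarged six-fold for this analysis; with no SD or formula given, that remains an inference, and the size of the trial does not settle the form of the model.

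The objection does not remove the core. The article does not leave the subgroup model open: it lists terms, and omits the ones that carry the subgroup question. Its stated rationale is that HbA1c is related to gender and age, which main effects would answer. The phrase "to examine the effects of the programme across different population subgroups" belongs to the separate exploratory set (ethnicity, diabetes duration, baseline HbA1c, education, insulin use). For cost, the article does name a difference-in-difference analysis, so it can state a treatment-by-time contrast where one is meant. And its one provision for interactions lets the data decide them.

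**Conclusion.** The point holds in a limited form. The listed terms do not include the treatment-by-sex and treatment-by-age contrasts that a pre-specified subgroup analysis needs, and the rule for interactions does not guarantee that they will enter. This rests on the text alone.

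The time term needs repair on either reading. With stacked rows and no treatment-by-time term, a true -0.50 appears as -0.25 when the arms start equal, and a baseline difference of +0.3 that persists in full turns it to +0.05. With baseline as a covariate, these figures do not apply and time is redundant. The article does not say which is meant, so the figures are conditional.

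The primary comparison is not affected: its stated model adjusts endpoint HbA1c for baseline and has no time term.

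**What to change.** Use the primary model for the subgroup analysis: endpoint HbA1c on baseline HbA1c and arm, with the covariates chosen for that model, plus sex, age group, arm x sex and arm x age group. Add arm x age group x sex, with the lower-order sex x age group term, if effects in the six cells are to be reported. Force these terms in and state that neither the data-driven selection nor the stepwise rule applies to them. Report the arm effect with a confidence interval in each subgroup, and name the interaction tests as the family under the false discovery rate correction.

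If a repeated-measures form is kept, use arm x time x subgroup with all lower-order terms and allow for within-patient correlation.

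The cost is a few sentences and a few lines of code, with no new data. The small downside is power. Under the assumptions above, comparing one cell with another has 63% power for a difference of 0.50 and a three-way contrast 37%, against 90% for the arm effect within a cell. The arm x sex and arm x age contrasts match or exceed 90% only for a difference as large as the whole target effect. The text should say this, so that a non-significant interaction is not read as evidence of equal effects.
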